**Internet-delivered Cognitive Behavioural Therapy for Adolescents with Obsessive-Compulsive Disorder: a pilot study**

## **1. Background**

Obsessive-Compulsive Disorder (OCD) is characterized by obsessive thinking and/or compulsive behaviours (American Psychiatric Association, 1994). OCD affects between 0,5 (Flament et al., 1988) and 2 % of children (Angst et al., 2004; Valleni-Basile et al., 1994). Paediatric OCD is commonly associated with severe impairments in academic, social and family functioning (Valderhaug & Ivarsson, 2005) and increases the risk of future mental health problems in adulthood (Wewetzer et al., 2001). As OCD frequently debuts in childhood, early intervention is crucial for long-term outcome and prevention of chronicity (Micali et al., 2010). Unfortunately, OCD is rarely adequately treated until adulthood as a result of combined factors, such as poor diagnostic detection, ineffective treatments and patients delay (Pinto, Mancebo, Eisen, Pagano, & Rasmussen, 2006). Availability of proper assessment and treatment differ both locally and regionally (Goodwin, Koenen, Hellman, Guardino, & Struening, 2002) and a majority of cases are not detected by health care (Wahl et al., 2010). In addition, recognized cases of OCD are seldom treated with effective psychological interventions (Valderhaug, Götestam, & Larsson, 2004). As a result, many patients' suffering is prolonged. For instance, one study of a clinical sample found that the mean time from OCD symptom onset (12 years of age) to receiving effective treatment was on average 17 years (Pinto et al., 2006).

### **1.1. Treatment of OCD**

Cognitive behaviour therapy (CBT) is recommended as the first-line treatment for paediatric OCD in the national guidelines of the Swedish National Board of Health and Welfare (Socialstyrelsen, 2009). Meta-analyses have repeatedly shown that CBT is an effective treatment for paediatric OCD with remission rates about 70% and an average symptom reduction of 40 - 64% (Abramowitz, Whiteside, & Deacon, 2000; Reynolds, Wilson, Austin, & Hooper, 2012; Watson & Rees, 2008).

Pharmacological treatment with serotonin reuptake inhibitors (SRIs) is an alternative or supplement to CBT. SRIs are an effective treatment for the condition, with a reduction of symptoms of 30 – 40% (Geller et al., 2003; Watson & Rees, 2008).

#### **1.1.1. Internet-delivered CBT and treatment of anxiety disorders**

Internet-delivered CBT (ICBT) is a new way of increasing CBT accessibility and treatment capacity. The treatment content is not different from regular CBT but the way of delivery. In ICBT, the patient works with web-based treatment material and homework assignments that are examined by a therapist via email and telephone. ICBT have been found to be effective in the treatment of adults with depression and anxiety disorders ([name] et al., 2005; Bergström et al., 2010; Hedman, Andersson, Ljótsson, et al., 2011; Spek et al., 2007). Studies have not only proved

internet-based treatments' efficiency compared to waitlist control, but have also been able to show results comparable to standard face-to-face treatment (Bergström et al., 2010; Hedman, Andersson, Ljótsson, et al., 2011). The research teams of [name], [name] and [name] have published several controlled studies on ICBT for adults ([name], 2009; Hedman, Andersson, Andersson, et al., 2011; Hedman, Andersson, Ljótsson, et al., 2011; Schneider, [name], Marks, & Bachofen, 2005). Andersson et al recently published the first controlled trial on ICBT for adults with OCD (E. Andersson et al., 2012). The Internet psychiatry unit at Karolinska University Hospital has since 2007 successfully implemented ICBT for depression and anxiety disorders within public health care.

**Internet-delivered treatment for children and adolescents:** ICBT has been found to be effective for various anxiety disorders for children aged 7 to 14 years (S. March, Spence, & Donovan, 2009). Though, to our knowledge there is no published data on ICBT and paediatric OCD.

To summarize, paediatric OCD is a serious psychiatric disorder that commonly is associated with significant impact on the individual's well-being and quality of life. CBT is effective for the majority of cases and is recommended as the first-hand intervention for treatment. Unfortunately accessibility to CBT is limited. Internet-delivered interventions have the potential to increase availability and range of effective psychological treatment for children and adolescents. ICBT has been shown to be effective in adults with various psychiatric conditions and children with anxiety disorders.

In Sweden, internet-based treatments for adolescents are not yet available within public health care. Our research group is currently studying an ICBT-intervention for anxiety disorders among Swedish children 8 to 12 years. A technical platform and ICBT protocol has been developed ([www.bup.se/bip](http://www.bup.se/bip)) and publication of first results are expected in 2013. We now want to expand ICBT interventions to adolescents with OCD.

## **2. Objective**

The overall purpose is to develop and test the feasibility, acceptability and efficacy of ICBT for paediatric OCD. In this pilot we want to test the technical platform, treatment manual and its efficacy. The efficacy of ICBT will be studied using quantitative method with robust psychometric scales addressing symptoms of OCD and comorbidity. The feasibility and acceptability will be addressed using a qualitative research method.

### **3. Method**

#### **3.1. Subjects**

Inclusion of participants compromise the following criteria:

- a primary diagnosis of OCD as defined by DSM-IV TR
- a total score of above 15 on the CY-BOCS
- age between 12 and 17 years
- ability to read and write Swedish
- daily access to the internet
- a parent that is able to co-participate in the treatment
- Participants on psychotropic medication must have been on a stable dose for the last 6 weeks prior to baseline assessment
- signed informed consent

Subjects will be excluded if:

- diagnosed autism spectrum disorder, psychosis or bipolar disorder
- suicidal ideation
- ongoing substance dependence
- subject not able to read or understand the basics of the ICBT self-help material
- completed CBT for OCD within last 12 months (defined as at least 5 sessions CBT including exposure and response prevention)
- ongoing psychological treatment for OCD or another anxiety disorder

#### **3.2. Measures**

The measures in this study have been chosen with respect to diagnostic accuracy as well as earlier findings on moderators and predictors of pediatric OCD treatment (Ginsburg, Kingery, Drake, & Grados, 2008).

##### **1.1.2. Diagnostic and symptom severity measures**

*Mini International Neuropsychiatric Interview for Children and Adolescents, MINI-KID* (D V Sheehan et al., 1998) is a short structured diagnostic interview for DSM-IV and ICD-10 psychiatric disorders in children and adolescents. MINI-KID is a reliable diagnostic instrument and is validated against the widely used MINI-KID-PL interview (D V Sheehan et al., 2010).

*Children's Yale Brown Obsessive Compulsive Scale, CY-BOCS* (Scahill et al., 1997). CY-BOCS is a semi-structured clinician administered interview and considered the golden standard in assessment

of OC symptom severity in children and adolescents. CY-BOCS has high internal consistency, good to excellent inter-rater agreement and correlates significantly with self-ratings of OC symptoms (Scahill et al., 1997). CY-BOCS will be the primary outcome measure.

*Clinical Global Impression – Severity, CGI-S* (National Institute of Mental Health, 1985). CGI-S is a brief clinician rating of symptom severity. Ratings on the seven graded scale range from 1 = “no symptoms” to 7 = “extreme severe”. CGI-S correlates highly with the CY-BOCS total score ( $r = .75$ , Storch et al., 2004).

*Clinical Global Impression - Improvement, CGI-I* (Guy, 1976). CGI-I is a brief clinician rating of the patients symptom severity change relative to the basement assessment. The seven graded scale ranges from 1 = “very much improved” to 7 = “very much worse”.

*Children’s Global Assessment Scale (CGAS, Shaffer et al., 1983)*. CGAS is a widely accepted instrument to quantify the overall level of functioning in children and adolescents. The 100-point scale is clinician rated and has demonstrated to have good discriminant and concurrent validity (Shaffer et al., 1983) as well as moderate inter-rater reliability in naturalistic settings (Lundh, Kowalski, Sundberg, Gumpert, & Landén, 2010).

### **1.1.3. Self-report measures**

All self-report measures will be internet-administrated.

The *Children’s Obsessional Compulsive Inventory Revised*, (CHOCI-R, Shafran et al., 2003) is a self- and parent-report measure of paediatric OCD symptom severity. The CHOCI-R has good internal consistency and correlates significantly with the CY-BOCS (Uher, Heyman, Turner, & Shafran, 2008).

*Child Obsessive-Compulsive Impact Scale – Revised* (COIS-R, Piacentini, Peris, Bergman, Chang, & Jaffer, 2007) is a self-report scale of OCD symptom impact on everyday life. COIS-R is available as a youth and parent version.

*Spence Child Anxiety Scale – Child and Parent version* (SCAS/P, Spence, 1998) will be used as a child and parent self-report measure of anxiety related psychopathology. The 45 items of the SCAS/P result in 6 subscales: panic attacks and agoraphobia, separation anxiety, physical injury fears, social phobia, obsessive-compulsive and generalized anxiety.

Symptom severity of depression in the adolescent will be assessed with *Child Depression Inventory* (CDI, Kovacs, 1985).

*Strengths Difficulties Questionnaire* (SDQ, Goodman, 1997) is a widely used self- and parent-report behavioral screening questionnaire with six subscales: emotional problems, conduct

problems, hyperactivity-inattention, peer problems, prosocial behavior.

*Patient Health Questionnaire* PHQ-9 (Kroenke, Spitzer, & Williams, 2001) is a brief self-report measure of depressive symptoms in adults. PHQ-9 will be used to measure parental depressive symptoms.

*GAD-7* (Spitzer, Kroenke, Williams, & Löwe, 2006) is a brief self-report measure of symptoms of general anxiety in adults. GAD-7 will be used to measure symptoms of anxiety in the parents.

*Obsessive Compulsive Inventory – Revised* (OCI-R, Foa et al., 2002) is a reliable and valid 18-item self-report scale for screening of OCD in adults and will be used to measure parental OC symptoms of both parents.

*Family Accommodation Scale, Parent-Report* (FAS-PR, Flessner et al., 2009). Originally a clinician-rated instrument (Calvocoressi et al., 1999), the parent-report version of the FAS consists of 12 items focusing on accommodation behaviors of parents with a child with OCD. Parental and family accommodation in OCD is expected to be a predictor of treatment outcome (Garcia et al., 2010). FAS-PR will be filled out by both parents.

*Adverse events assessment.* During the treatment phase of the study participants will be asked to fill in a web-based form on the occurrence of any adverse events as a reaction to or consequence of the treatment. Adverse events frequency will be reported in the publication of the study.

In the self-report procedure parents will even be asked to answer questions about parental educational level and gross household income, ethnicity of adolescent and parents and other demographic data. Moreover, participants will be asked about prior treatment history (e.g. previous CBT or medication) and response to previous treatments. Table 1 gives an overview of the measures that will be used in the study. Attachment 1 displays an overview of which measures are used when in the study.

Table 1: List of measures

| Category                        | Clinician assessed                          | Self-report adolescent | Self-report parent                                       |
|---------------------------------|---------------------------------------------|------------------------|----------------------------------------------------------|
| Demographics             | Age
Sex
Family structure              |                        | Educational level
Gross household income
Ethnicity |
| OC symptom severity      | CY-BOCS
CGI-S
CGI-I                   | CHOCI-R
COIS-R      | CHOCI-R
COIS-R                                        |
| Comorbidity              | MINI-KID                                    | SCAS
SDQ
CDI     | SCAS
SDQ                                              |
| Global functioning       | CGAS                                        |                        |                                                          |
| Parental psychopathology |                                             |                        | GAD-7
PHQ-9
OCI-R                                  |
| Family factors           | Family history of OCD
/ other diagnosis? |                        | FAS-PR                                                   |

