### **1.2.4. Treatment**

When completed the self-report measures adolescents and parents will be provided with login information for the ICBT treatment platform. Adolescents and parents will have separated login accounts. From the start of treatment participants will have full-scale access to the internet treatment for 12 weeks, which includes materials, interactive scripts and mail contact with a clinician. After 12 weeks participants will have access to treatment materials, but it will not be possible to unlock new parts of the treatment or to have email contact with the clinician.

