### **1.2.6. Safety procedures**

Clinicians that suspect any kinds of adverse events under the assessment or treatment process contact the parent and adolescent via telephone as a first step of assessing the severity of the incident. Adverse events in this context is defined as an actual or potential situation that threaten the patients well-being e.g. suicide risk. In the case of an adverse event the clinician informs the study coordinator (FL) for discussion of adequate action taking. If prolonged ICBT treatment is considered inappropriate with regard to the participants' best interest and well-being the participant is excluded from the study and both parent and adolescent provided with proper referral information. Any adverse events will be reported in the planned publication of the pilot study.

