### **1.2.8. Post-treatment measurement and follow-up**

Post-treatment measurement with clinician rated symptom severity (face-to-face interview with CY-  
Project plan BiP OCD, version 2014-12-16

BOCS, CGI-I, CGI-S and CGAS) as well as self-report measures will be conducted immediately after treatment, latest within 4 weeks after treatment protocol is finished.

Follow-up measurements will be performed at 3, 6 and 12 months after treatment. At follow-up CY-BOCS, CGI-I, CGI-S and CGAS will be administrated over the phone by a clinician. Self-report measures will be administrated via the internet.

Succeeding completed follow-up all participants will be contacted by the clinician via the ICBT platform and offered an ICBT booster session. Thus, standardized booster sessions will be offered at 3, 6 and 12 months after treatment. During follow up, participants are asked whether they are willing to participate in the qualitative interview study. Participants give consent to this study on a separate form.

[figure not shown]

Figure 1: Procedures flow chart

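### The protocol describes adverse events in two unreconciled ways, does not say which supplies the published frequency, and limits the participant form to treatment-attributed events during the 12 treatment weeks

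*Protocol*

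**What the plan says.** Adverse events appear in two places in the protocol.

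- **Section 1.1.3 (Self-report measures), paragraph on adverse events assessment.** The tool is a web form for participants. Its timing is "During the treatment phase of the study participants will be asked to fill in a web-based form", and its content is limited to events that the reporter links to treatment: participants are to "fill in a web-based form on the occurrence of any adverse events as a reaction to or consequence of the treatment". The next sentence reads "Adverse events frequency will be reported in the publication of the study".
- **Section 1.2.6 (Safety procedures).** The channel is the clinician: "Clinicians that suspect any kinds of adverse events under the assessment or treatment process contact the parent and adolescent via telephone". The definition is "Adverse events in this context is defined as an actual or potential situation that threaten the patients well-being e.g. suicide risk". The section ends with "Any adverse events will be reported in the planned publication of the pilot study".

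On timing, section 1.2.4 states that "participants will have full-scale access to the internet treatment for 12 weeks", after which e-mail contact with the clinician ends. Section 1.2.8 states that "Follow-up measurements will be performed at 3, 6 and 12 months after treatment", with clinician ratings by telephone, self-report over the internet and a booster session offered each time. It does not mention the adverse event form.

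**The concern.** What counts as an event, who reports it and when it is asked about have to be settled before data are collected. An event that was never recorded cannot be recovered by any later analysis, so this is not a detail that can wait for an analysis plan.

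Two features of the form matter. First, the reporter must judge causality before anything is written down. Worsening or a new difficulty that an adolescent puts down to the OCD, or to something else, need not be entered. The trial is open and single-arm (section 1.4), so no control group can later separate treatment effects from the course of the illness. Second, the form is described only for the treatment phase, while contact with the intervention continues through the booster sessions.

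At stake is whether the promised frequency can be interpreted. Section 1.1.1 knows of no published data on internet-delivered CBT in paediatric OCD, so the harms reported here are among the first a reader will have.

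**Working it through.** The documents give no adverse event rate, expected count or safety precision, so there is no stated figure to reproduce. The check is a comparison of the text, with one piece of labelled illustration.

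**1. The two descriptions side by side**

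| | Section 1.1.3 | Section 1.2.6 |
|---|---|---|
| Who reports | Participant, web form | Clinician, on suspicion |
| Causal condition | Attributed to treatment | None |
| Potential events | Not mentioned | Included |
| Threat to well-being needed | No | Yes |
| When | Treatment phase | Assessment or treatment process |
| Promise | Frequency published | Any event published |

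Neither set contains the other. A mild reaction attributed to treatment that threatens nobody's well-being fits only 1.1.3. A suicide risk unrelated to treatment fits only 1.2.6. No section says which column supplies the frequency, or how an event seen through both channels is counted.

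**2. The collection window**

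Inputs: 12 treatment weeks (section 1.2.4) and follow-up to 12 months, taken as 52 weeks (section 1.2.8).

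12 / (12 + 52) = 12 / 64 = 18.8%

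This is the share of calendar time in which the form is said to be in use. It is not the share of events captured, since full treatment access falls within those 12 weeks.

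**3. What the causal wording could do to the form's count (all rates assumed)**

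Let n = 27 (section 1.4), q = the proportion of participants with any event, and a = the proportion of those who attribute it to treatment. Then the expected number with any event is n × q, and the expected number recorded on the form is n × q × a.

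| q | n × q | a = 0.25 | a = 0.50 | a = 0.75 |
|---|---|---|---|---|
| 0.10 | 2.7 | 0.7 | 1.4 | 2.0 |
| 0.20 | 5.4 | 1.4 | 2.7 | 4.1 |
| 0.40 | 10.8 | 2.7 | 5.4 | 8.1 |

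The form alone would show between 0.7 and 8.1 participants where 2.7 to 10.8 had an event. The range is wide because q and a are unknown. It concerns the form only: clinician-detected events would add to it, and counting potential situations could raise a combined total further.

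**4. A figure that does not measure this defect**

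If no events were reported in 27 participants, the one-sided 95% upper limit for the true rate would be 1 − 0.05^(1/27) = 10.5%. That follows from n alone and would be the same after the form was reworded. Assuming that half of events are captured gives 10.5% / 0.5 = 21%, but the 50% has no source in the protocol and the step supposes that the clinician channel finds nothing.

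**The case against.** The strongest reply is that the two sections do different jobs. Section 1.2.6 limits its definition to its own context: it governs when a clinician telephones the family and informs the study coordinator. Section 1.1.3 describes a self-report measure of perceived treatment reactions. A narrow measure and a broad safety trigger can coexist. This stands, and a reader who infers that the definitions are incompatible goes too far: they are different and unreconciled.

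A reader might also infer that the published frequency will be too low. The text does not show that. The clinician channel has no causal filter, includes potential situations, may extend to follow-up assessments, and comes with a promise to publish any event. If it is counted, the total could rise. Equally, nothing states that the two channels are pooled.

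Other measures would also show some deterioration. CHOCI-R is collected weekly from child and parent (section 1.2.5). CY-BOCS, CGI-I, CGI-S and CGAS are rated by a clinician at post-treatment and at three follow-ups, and the self-report measures are repeated (section 1.2.8). These soften the concern but do not replace an event record. The clinician channel still rests on suspicion, with no systematic enquiry described, and e-mail contact ends at week 12.

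Finally, neither the form nor Attachment 1, which sets out the timing of measures, is at hand. The form's items may be broader than the sentence describing it, and the schedule may place it at later visits. The point rests on the description in the text.

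**Conclusion.** The point holds in a limited form. The protocol uses two different descriptions of adverse events and does not name the source of the frequency it promises. As described, the participant form is likely to under-record events of all causes and does not systematically cover the follow-up year. For the published total, the direction of any bias depends on whether clinician-detected events are included, and its size cannot be computed from the document. The 18.8% of calendar time describes the window and nothing more.

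This assumes that the form asks what section 1.1.3 says it asks, and that Attachment 1 does not add it to later assessments. It ranks as a cheap improvement and does not affect the primary CY-BOCS outcome.

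**What to change.** 1. In section 1.1.3, reword the form to ask about any new or worsened problem regardless of suspected cause, with relatedness rated as a separate item.
2. Keep the form in the treatment phase, and add it to the internet assessments already scheduled at post-treatment and at 3, 6 and 12 months.
3. State what the published frequency is: participants with at least one event, all-cause and treatment-related separately, with clinician-detected events identified by source.
4. Leave the escalation trigger in section 1.2.6 unchanged, and add a sentence saying how it relates to the recording definition. Carrying the recording definition over to that section would alter a safety procedure for no statistical gain.

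For data already collected, the two channels can still be reported separately, each with its own definition and window.

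The cost is a rewritten paragraph, one linking sentence and an existing form at assessments that already take place. The downside is a longer list of events, many of them unrelated to treatment.
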